### Observational Pharmacokinetic and Pharmacodynamic Study

A total of 10 mL of peripheral blood samples will be collected for up to a maximum of 8 samples per patient or until PKI is stopped at an unselected time after the last PKI intake. The blood samples will be centrifuged, the plasma will be frozen and stored until PKI levels are measured, and the dry pellet will be analyzed for the exploration of genetic variants involved in PKI pharmacokinetics. Moreover, for patients who accept, 6 × 5 mL blood samples will be collected over a maximum of 12 hours during one visit to the hospital. Specific information on pharmacokinetic data will be collected at each blood draw, and all relevant clinical and biological information will be obtained from the medical files of the patients (detailed in the *Collection and Management of Data* section).

### Outcomes

#### Primary Outcomes: Randomized Controlled Medication Adherence Study

The primary outcome was global adherence, defined as the percentage of days with correct medication use of each subject. The sample size was calculated to ensure sufficient power to test the difference in the mean logit global adherence between groups (see the *Sample Size* section). Medication adherence will also be compared between groups following the three operational definitions defined by the EMERGE (European Society for Patient Adherence, Compliance, and Persistence Medication Adherence Reporting Guideline) guidelines: implementation of treatment during the persistent period (daily management of oral targeted anticancer drugs), persistence with treatment (the distribution of times between enrollment and discontinuation), and longitudinal adherence (the product of persistence and implementation) [14,28,29].

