#### Assignment of the Intervention

The collection of adherence data patterns in both groups at baseline is crucial to check whether adherence patterns are homogeneous between the groups before the intervention starts. In both groups, patients will use an electronic monitor for at least 21 days before randomization. At the end of the baseline period, the patients will be randomized 1:1 to either attend the medication adherence program (intervention group) or be part of the standard of care (control group; Figure 1). The randomization lists will stratify participants according to their cancer type and the time elapsed between PKI initiation and the time of inclusion (less or more than 30 days). The randomization sheet lists 1 (intervention group) or 0 (control group) and will be provided by an independent researcher from the Unisanté Research Support Unit. The randomization list established by Excel (version 2016, Microsoft) will be based on variable size block randomization to prevent predictability and ensure a balanced allocation to each group. After randomization, the patient, research team, pharmacy, and clinical team will all be aware of the assigned group.

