### Sample Size

#### Randomized Controlled Medication Adherence Study

We assumed that the mean longitudinal adherence will remain stable at 95% in the intervention group during the follow-up period, whereas it would decrease from 95% to 80% in the control group during the 340 days from randomization to the end of follow-up. We also assumed an SD for the logit of longitudinal adherence of 1.8, for both groups and at all timepoints. This corresponds to 95% individual adherence in the intervals 10%-99.3% and 35%-99.9% in the control and intervention groups, respectively, at the end of follow-up. A sample size calculation was performed to simulate individual series of daily medication (1=at least the correct number of daily openings of the electronic monitor; 0=fewer daily openings than prescribed) according to the above parameters to consider both the interindividual variability (SD 1.8) and the intraindividual variability (the measurement error). Considering that the number of measures of a subject will be 340 and assuming a 10% dropout in the middle of the year, 120 patients must be included in the study (60 in each group) to reach a power of 80% with a .05 significance level when comparing the mean of the logit of global adherence between groups using a two-tailed Student *t* test. Differences are considered statistically significant if *P*<.05.

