### Data Analyses

#### Medication Adherence Analysis

Adherence to PKI will be assessed using electronic monitor, calculated pill counts, and patient reports. Medication behavior will be described with a binary variable (1=at least the correct number of daily openings of the electronic monitor; 0=fewer daily openings than prescribed) in each group. This coding method is commonly used; however, this code cannot discriminate overadherence, which is considered in the same way as optimal adherence. The implementation will be described in each group using generalized estimating equation models; persistence with PKI (ie, adherence until PKI discontinuation) will be represented using a Kaplan-Meier survival curve [14]. Global adherence will be estimated in each group with the proportion of patients with correct medication taking, defined as ≥95% days with correct dosing during days 1 to 360, compared between groups using a chi-square test. As ≥95% days with the correct dosing threshold is an assumption, we will perform sensitivity analysis with other thresholds such as 90%, 85%, and 80%. Multivariate logistic regression models will be used to evaluate whether any detected effect of the intervention remained after adjusting for potential sociodemographic or clinical confounders. As a secondary analysis, the difference in medication taking will be explored across genders.

A systematic computerized term search in the adherence reports of the intervention group will be performed to identify the most frequent variables affecting PKI adherence, and a regression model will be used to discover their association with adherence [35].

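### Persistence is timed from enrollment rather than randomization, and the 360-day adherence window has no defined start and does not match the 340-day follow-up

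*Protocol article*

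**What the plan says.** Four places in the protocol article bear on the time origin.

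- Assignment of the Intervention: in both groups "patients will use an electronic monitor for at least 21 days before randomization". The stated purpose is to check that adherence patterns are alike before the intervention begins. Randomization follows at the end of this period.
- Primary Outcomes: one of the three operational definitions is "persistence with treatment (the distribution of times between enrollment and discontinuation"). Longitudinal adherence is the product of persistence and implementation.
- Sample Size: the control group is assumed to decline "during the 340 days from randomization to the end of follow-up", with 340 measures per subject.
- Medication Adherence Analysis: the global adherence proportion, compared by chi-square test, counts patients with "≥95% days with correct dosing during days 1 to 360". Day 1 is not defined here or elsewhere.

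Three further statements matter. Enrollment of Participants says that a patient whose PKI is stopped, or changed to a non-PKI treatment, leaves the study, with data kept. The section on instruments gives 12 months of monitoring, or until the PKI is stopped. The section on the interviews places them over 12 months.

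**The concern.** A randomized comparison should start its outcome clock at randomization. Time before that cannot show an effect of the program, because nobody has yet been assigned to it.

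For persistence, the stated origin lies before randomization, and reaching randomization requires still being on a PKI. The start of each patient's curve is therefore event-free by construction. The baseline lasts at least 21 days, so the length of that stretch can vary between patients. Persistence at any given month is read too high, and longitudinal adherence inherits the error.

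For global adherence, the 360-day window and the 340-day follow-up cannot both be right as written. If the window starts with the monitor, baseline days enter both numerator and denominator and pull the arms together. They also fall within the first 6 weeks, when the Limitations section expects monitoring itself to improve behaviour.

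**Working it through.** **1. Which origin fits 360 days?** From monitor start: 21 + 340 = 361, close to 360 and to 12 months of monitoring. From randomization: 360 − 340 = 20 days beyond the planned follow-up. The first fits better, but the text does not settle it. Either way the two sections disagree.

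**2. Persistence.** Let S(t) be persistence from randomization and L the lead-in. With a constant L, the curve from enrollment is 1 for t < L and S(t − L) afterwards: the true curve moved to the right. To illustrate the size, take the 85% 12-month persistence of the feasibility study and assume a constant discontinuation hazard, a 360-day year and L = 21. The curve from enrollment then reads 0.85^(339/360) = 85.8% instead of 85.0%, about 0.8 points too high. With an assumed 70% instead, 0.70^(339/360) = 71.5%, about 1.5 points too high. The shift is the same in both arms.

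**3. Reproducing the planned power.** Inputs from Sample Size: 95% constant in the intervention group, 95% falling to 80% in the control group, SD 1.8 on the logit scale, 340 daily measures, 10% dropout at mid-year, "120 patients must be included in the study (60 in each group"), "to reach a power of 80% with a .05 significance level", for "comparing the mean of the logit of global adherence between groups using a two-tailed Student *t* test".

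Closed form: mean control adherence (95 + 80)/2 = 87.5%; logit(0.95) − logit(0.875) = 2.944 − 1.946 = 0.999. This gives 52 per arm, and 52/0.9 rounds up to 58, close to the 60 stated. Simulation (3000 trials; control decline linear in probability; subject effect constant over time; 0.5 added in the logit) gives a difference of 0.92, SD 1.76 and power of 81%. The stated 80% is reproduced for a 340-day window from randomization.

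**4. Adding baseline days.** Assume 95% adherence during baseline in both arms. The mean gap over 340 days is 95 − 87.5 = 7.5 points; over 20 + 340 days it is 7.5 × 340/360 = 7.1 points. Baseline share: 20/360 = 5.6%.

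| Window (decline linear in probability) | Logit difference | t-test power | ≥95% proportions | Chi-square power |
|---|---|---|---|---|
| 340 days from randomization | 0.92 | 81% | 50.8% v 30.2% | 64% |
| 20 baseline + 340 days | 0.88 | 77-78% | 50.6% v 31.0% | 59% |
| 21 baseline + 339 days | 0.86 | 75.5% | 50.4% v 31.2% | 58.5% |

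A separate simulation with 21 baseline days added gave 79.9% falling to 77.0% (t test) and 63.2% falling to 59.8% (chi-square). Simulation error is about 0.7 points for the t test: √(0.8 × 0.2/3000) = 0.007.

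**5. Sensitivity to the shape of the decline.** If the control decline is linear on the logit scale, t-test power is 66% over 340 days and 63-65% with baseline days included; chi-square power is 49% in each case. The plan's 80% is not reproduced under this shape, and the loss from baseline days is smaller.

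**The case against.** The strongest reply is that day 1 is undefined, so a reader who infers that days 1 to 360 certainly include the baseline goes beyond the text. The interviews run over 12 months and can begin only after randomization, so 360 days could be meant as a year from randomization. That stands. It changes the problem from dilution to a window longer than the planned 340 days; it does not remove the conflict.

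A reader might also infer that the planned t test loses power. The 360-day window is attached only to the ≥95% chi-square analysis. The only window given for the t test is the 340 days from randomization, so its loss is conditional.

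It would be wrong to call the baseline untreated time: patients take their PKI throughout and are merely not yet exposed to the program. Nor do the documents support a much longer baseline taking up a large share of the window. The quarterly visits in the Limitations section describe interview frequency, and a long baseline would break the 21 + 340 arithmetic that points to monitor start in the first place.

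On persistence, no test is named, and a constant lead-in leaves the log-rank ordering unchanged. The harm is to the absolute level, not to the fairness of the comparison. The power loss is also small beside the 81% versus 66% that depends on the shape of the decline alone. About 64 to 66 per arm would restore 80%, and 130 patients are reported in the adherence study, though the number randomized is not given.

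**Conclusion.** The point holds in two limited parts.

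First, persistence has the wrong origin on the face of the text. Randomized patients carry a guaranteed event-free lead-in of at least 21 days, which overstates absolute persistence and longitudinal adherence in both arms without favouring either. The overstatement is about 1 point at 12 months in the illustrations above, which assume a constant hazard and the minimum baseline.

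Second, the 360-day window and the 340-day follow-up are unreconciled, with day 1 undefined. If baseline days are counted, the effect is a modest dilution toward the null: about 4 to 5 points of chi-square power, and about 3 points of t-test power if the same window were applied there (up to about 5 with 21 + 339 days). These figures rest on a control decline linear in probability and 95% baseline adherence in both arms; with a decline linear on the logit scale the loss is smaller.

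This should be corrected, but it does not threaten the validity of the randomized comparison.

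**What to change.** - State that time zero is randomization for global adherence, implementation, persistence and longitudinal adherence.
- In Primary Outcomes, replace enrollment with randomization as the start of persistence.
- In Medication Adherence Analysis, replace the 360-day window with days 1 to 340 after randomization, or to the end of monitoring if that comes earlier. The second clause is needed because a patient with a longer baseline may not have 340 days left if the 12 months of monitoring run from inclusion.
- Keep baseline days out of every outcome. Use them for the homogeneity check already planned and, optionally, as a covariate.

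The cost is wording. Monitor openings are stored with date and time, so the clock can be reset without new data, and the article places the final analysis in 2022, after data collection.

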#### Secondary Outcomes: Pharmacokinetic and Pharmacodynamic Data

The plasma concentrations of the PKI and active metabolites, if appropriate, will be measured using validated methods of liquid chromatography-tandem mass spectrometry for each blood sample collected [30,31]. Internal standards will be used to optimize the analytical accuracy and precision of the method, essentially by abrogating the influence of matrix effects and inherent variability in the extraction procedure. The pharmacokinetic variables quantifying PKI exposure will then be calculated from population-based individual Bayesian pharmacokinetic parameters and expressed as the area under the curve and trough drug concentrations (minimum drug concentration) [32]. The efficacy of anticancer drugs will be expressed as progression-free survival, which is the time interval between PKI initiation and the date of tumor progression, defined according to the standardized criteria *Response Evaluation Criteria In Solid Tumors* [33], or death from any cause. If a patient is event-free (progression or death), the time will be censored at the last follow-up visit, the end of the study follow-up, or treatment discontinuation. The response to treatment will be assessed according to local standards, usually every 3 months, using a computed tomography scan or positron emission tomography scan. In addition, an overall survival analysis will be undertaken in an exploratory manner. The toxicity of PKI will be assessed according to the National Cancer Institute–Common Terminology Criteria for Adverse Events [34].

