### Enrollment of Participants

This translational study will be conducted at the Medical Oncology Service of the Department of Oncology of the Lausanne University Hospital (CHUV) outpatient clinic (Lausanne, Switzerland) in collaboration with the Community Pharmacy of the Center for Primary Care and Public Health Unisanté (Lausanne, Switzerland) and the Center for Research and Innovation in Clinical Pharmacy Sciences (CHUV).

Adult patients aged >18 years who were treated with a PKI for solid tumors and followed at the CHUV were eligible to participate in this study. Participants with an inability to make decisions, with cognitive disorders, under tutelage, or not fluent in French or English or without the aid of an interpreter will be excluded from the study. Patients will be excluded solely from the medication adherence part of the study if they do not self-manage oral anticancer treatment (ie, nursing homes and home care services) or if they are already enrolled in an interventional study. If one PKI is switched to another PKI during the study, the patient will continue to participate in the study. However, if the PKI treatment is stopped or changed to a non-PKI anticancer treatment, the participant exits the OpTAT study; but, the data collected are kept for analysis.

The OpTAT study is voluntary, and patients will need to sign an informed consent form to participate in the medication adherence study, the pharmacokinetic and pharmacodynamic study, or both. The recruitment of participants began in May 2015. It ended in March 2021 for the medication adherence part but is ongoing until December 2021 for the pharmacokinetics part.

Oncologists were asked to refer eligible patients to a pharmacist PhD student or to the research staff from the Center of Experimental Therapeutics (CHUV), who will present the informed consent form to the patient after the medical visit. The participants will follow their treatment as usual, and no changes in the usual medical procedure will be made. No payment or compensation will be provided to the patients or to the oncologists as the patients are being seen as part of their routine follow-up clinical care.

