#### Relationships Between PKI Exposure, Efficacy, and Toxicity

The correlation between PKI exposure and efficacy will be explored using Cox regression analysis of progression-free survival. The correlation between PKI exposure and toxicity will be explored by pharmacokinetic and pharmacodynamic models using the software program NONMEM or by logistic regression analysis. Receiver operating characteristic analyses will be used to evaluate the best exposure threshold to predict clinical outcomes and performance (in terms of area under the receiver operating characteristics curve and sensitivity and specificity).

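### PFS is timed from PKI initiation while patients already on a PKI may enter late; without delayed entry, the exposure–PFS analyses count guaranteed survival on drug as time at risk

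*Protocol article*

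**What the plan says.** All references are to the protocol article.

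- **Time origin.** Under *Secondary Outcomes: Pharmacokinetic and Pharmacodynamic Data*, PFS is "the time interval between PKI initiation and the date of tumor progression" or death from any cause.
- **Censoring.** The same section says that for event-free patients "the time will be censored at the last follow-up visit, the end of the study follow-up, or treatment discontinuation". These rules all concern the end of observation. None says when a patient starts to be observed.
- **Eligibility.** Under *Enrollment of Participants*: "Adult patients aged >18 years who were treated with a PKI for solid tumors and followed at the CHUV were eligible". Nothing requires a new start, and prior PKI time has no upper limit. The rule covers both parts of the study.
- **Exit.** In the same section, "if the PKI treatment is stopped or changed to a non-PKI anticancer treatment, the participant exits the OpTAT study".
- **Late inclusion is expected.** Under *Assignment of the Intervention*, the randomized part stratifies on "the time elapsed between PKI initiation and the time of inclusion (less or more than 30 days"). The upper stratum is open-ended.
- **Exposure.** It is "calculated from population-based individual Bayesian pharmacokinetic parameters and expressed as the area under the curve and trough drug concentrations", so it rests on samples drawn after consent.
- **Analysis.** Under *Relationships Between PKI Exposure, Efficacy, and Toxicity*: "The correlation between PKI exposure and efficacy will be explored using Cox regression analysis of progression-free survival". ROC analyses then look for the best exposure threshold. The article mentions no delayed entry, landmark or restriction to new starters.

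**The concern.** A patient who died, or who stopped the PKI after progressing, before inclusion can never give a study sample. For someone included months after starting, that interval was survived on a PKI by design. If it is counted as time at risk from initiation, the early risk sets are filled with people who could not have contributed an early death or a treatment-ending progression.

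Two things are at stake. First, the level of PFS is too favourable, and so is any binary outcome cut from it for a ROC analysis. Second, the exposure hazard ratio can be distorted if exposure differs between patients who have been on drug for a long and a short time. Relating concentration to response is a stated secondary objective, and the article wants the results to inform individual dosing, so the threshold analysis inherits either problem.

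**Working it through.** **Plan's own figure.** There is none to reproduce. The article gives no PFS median, hazard ratio (HR), event count or power. Every input below except the patient counts is an assumption, and the results show a range, not this trial's bias.

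**Risk sets.** Let e be the time from initiation to inclusion and t the PFS or censoring time, both from initiation.
- Naive risk set at time s: all patients with t ≥ s.
- Delayed-entry risk set at time s: patients with e < s ≤ t.

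**By hand.** Assume exponential PFS with a true median of 12 months and a patient included event-free at month 6. Residual PFS again has median 12, so counted from initiation this patient's median is 6 + 12 = 18 months. For a ROC outcome of an event by month 12, the true probability from initiation is 1 − 2^(−12/12) = 0.50. For this late entrant it is 1 − 2^(−6/12) = 0.29.

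**Level of PFS, with a true exposure effect.** I simulated 400,000 source patients per scenario. Assumptions: exponential PFS, two equal exposure groups, true HR 0.60 (high versus low exposure), 50% or 70% of source patients entering late with a mean delay of 3 to 12 months, enrolment only if still event-free, and 24 months of follow-up after entry. The mildest and most severe late-entry scenarios for each median are:

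| True median (months) | Late share, mean delay | Naive median | Delayed-entry median | Naive HR | Delayed-entry HR |
|---|---|---|---|---|---|
| 5.92 | 50%, 3 months | 7.31 | 5.93 | 0.596 | 0.601 |
| 5.94 | 70%, 12 months | 9.64 | 5.96 | 0.543 | 0.594 |
| 11.89 | 50%, 3 months | 13.35 | 11.89 | 0.598 | 0.600 |
| 11.85 | 70%, 12 months | 18.55 | 11.83 | 0.575 | 0.601 |
| 23.85 | 50%, 3 months | 25.36 | 23.85 | 0.594 | 0.594 |
| 23.70 | 70%, 12 months | 31.66 | 23.74 | 0.593 | 0.606 |

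Inflation is the naive median divided by the true median, minus 1. For example, 7.31/5.92 − 1 = 23% and 9.64/5.94 − 1 = 62%. The ranges are 23–62%, 12–57% and 6–34% for true medians of about 6, 12 and 24 months. With no late entry the bias is zero.

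The HR moves modestly although exposure was not linked to entry time. The reason is selection: high-exposure patients survive to late entry more often (their share among those enrolled rises from 0.50 to as much as 0.55), so they carry more guaranteed time. A separate check at the 12-month median, expressed as low versus high exposure, agrees: true HR 1/0.60 = 1.67, naive 1.77, delayed entry 1.68.

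**Hazard ratio, with no true effect.** Assumptions: median 12 months, half the patients entering uniformly 0–24 months after start, 12 months of follow-up, and the probability of low exposure changing with time on drug up to 12 months. Ranges come from repeated simulations; type I error is at n = 250.

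| Low exposure, at start → at 12 months or more on drug | Naive HR (low vs high) | Delayed-entry HR | Naive type I error | Delayed-entry type I error |
|---|---|---|---|---|
| No change | 0.98–1.00 | not needed | 4.5% | not needed |
| 30% → 40% | 0.90–0.93 | 0.99–1.01 | 4.8% | not run |
| 20% → 50% | 0.74–0.76 | 0.99–1.00 | 25–27% | 4–6% |

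If half of those *enrolled*, rather than half of the source patients, are late, the last row becomes HR 0.70 versus 0.98 and type I error 40% versus 6.5%. At n = 51, the one per-drug count in the article (palbociclib), naive type I error is 4–6% in all three rows.

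**The case against.** The strongest reply is that the article is only silent. It names a Cox model without stating the risk set, PKI initiation is a legitimate origin, and a condensed article commonly leaves an entry-time argument to the full plan. Part of this stands: the article does not say that early time is counted as at risk, and a fuller plan may already handle it. But the origin, the event and the end-of-observation rules are all stated, and when applied as written to the population admitted they give a biased result. That is more than a missing detail.

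Several stronger readings are tempting, and the article does not support them.

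- *A reported median PFS will be overstated.* No PFS median or Kaplan–Meier estimate is planned; Kaplan–Meier is named for persistence only. The medians above show how far the time scale is distorted, not an error in a planned result.
- *The Cox analysis will find a spurious exposure effect.* With no true effect, this needs exposure to be related to time already on drug. The article gives no evidence for or against that.
- *Type I error is about 27%.* That needs the strong 20%-to-50% gradient and a pooled n of 250. The 250 are everyone with at least one sample, across 31 PKIs and their combination, while pharmacokinetic sizing is about 50 patients per PKI.
- *Late entrants must have been progression-free at inclusion.* Only being alive and on a PKI is required. Freedom from progression is an inference, and the simulations assume it.
- *The 30-day strata show how common late entry is in the pharmacokinetic part.* They belong to the randomized part. For the pharmacokinetic part, late entry follows only from the shared eligibility rule.

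**Conclusion.** The point holds in limited form. The stated PFS definition and open eligibility together put guaranteed survival on a PKI into the time at risk unless entry is modelled. Absolute PFS and PFS-based ROC outcomes are inflated whenever late entry occurs, by 6–62% of the median across the assumed scenarios. The exposure hazard ratio is affected mainly when exposure is related to time on drug: under no true effect, from about 1.00 (no relation) through 0.90–0.93 (weak) to about 0.75 (strong). A true effect shifts modestly even without such a relation. Delayed entry recovered the true value, within simulation error, wherever it was run.

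These sizes rest on exponential PFS, event-free status at entry, and assumed medians, delays and shares. The size in this trial cannot be derived. At about 50 patients per drug, type I inflation is not visible. The analysis is secondary and exploratory, so this is an improvement worth making and no threat to the primary comparison.

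**What to change.** - Keep PKI initiation as the time origin. State that patients join the Cox risk set at inclusion or first pharmacokinetic sample (left truncation).
- Use exposure known by that time, or time-updated exposure.
- Exclude patients whose progression preceded entry, or treat them as not at risk.
- Apply the same risk set to any ROC outcome derived from PFS.
- Add a sensitivity analysis in patients enrolled within 30 days of initiation, and report the distribution of delay from initiation to entry so that readers can judge the scale.

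The cost is a sentence or two in the analysis section and an entry-time argument in the model call. The initiation date is already needed for PFS, and inclusion and sample dates should already be on record. The downside is slightly less precision at early times, where fewer patients are at risk.
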